### Randomisation

An independent pharmacy assistant will allocate each patient based on computerized randomization lists to either receive placebo (saline) injection or triamcinolone acetate 40 mg injection IM. Randomization is stratified for setting (general practitioner and outpatient clinics of department of orthopaedics) and uses random blocks of 2 and 4.

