### Sample size

Data from the Qvistgaard et al. study (patients with hip OA from primary care and secondary care) were used to calculate our sample size [6]. That study showed a baseline standard deviation (SD) of 20 for pain at rest and at walking (0-100 visual analogue scale; VAS). Assuming a minimal clinically relevant difference of 10 points (effect size 0.5), 64 patients per group will be needed to show a statistically significantly difference using 80% power and with a 5% alpha.

In that same study [6] the WOMAC total score (0-96) was used with an SD of 15. Standardized to a 0-100 score this SD is almost 16. Assuming an SD of 16 and an 8-point difference as clinically relevant (effect size 0.5), the same sample size is needed.

We checked these scores in a Dutch study population with hip OA, i.e. those with a K-L score of the hip ≥ 2 and a VAS pain score ≥ 30, participating in the GOAL study [22]. This showed they had a mean VAS score of 56.4 with an SD of 19.3, a mean WOMAC pain score of 51.2 with a SD of 16.4; these data are very similar to the SDs in the study of Qvistgaard et al. Therefore, in the planned trial, we will include 135 patients, anticipating only 5% loss to follow-up based on the relatively short follow-up and earlier experience with loss to follow-up [22,23].

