### Data analyses

Data analysis will be performed based on the 'intention to treat' principle.

Descriptive statistics will be used to describe patient's characteristics, items of physical examination, and the severity of radiologic hip OA.

Linear mixed models will be used for repeated measures to analyze the continuous outcome measures. Fixed effects will be time, time by therapy and the covariates we adjust for. For patients lost to follow-up, we will include all observed data in the analysis. Adjustment will be made for those baseline variables that change the effect estimate by more than 10%. Similar analyses with Generalized Estimating Equations techniques for repeated measures will be done for dichotomous outcome measures.

Subgroup analyses for setting will be analyzed by assessing interaction effects between type of intervention and setting on the primary outcomes; in addition, the estimates will be shown for both settings separately. We realize that these subgroup analyses will remain solely explorative because our sample size is not directed to powerful subgroup analyses.

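### Setting, the stratification factor, is not a prespecified term of the main model and can enter only through a data-driven 10% rule that will usually omit it at the planned effect

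*Protocol article*

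**What the plan says.** Under Randomisation, the protocol article states: "Randomization is stratified for setting (general practitioner and outpatient clinics of department of orthopaedics) and uses random blocks of 2 and 4".

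Under Data analyses, it gives the terms of the linear mixed model for continuous outcomes: "Fixed effects will be time, time by therapy and the covariates we adjust for". It then says how those covariates are chosen: "Adjustment will be made for those baseline variables that change the effect estimate by more than 10" per cent. Dichotomous outcomes are to be handled in a similar way with generalized estimating equations (GEE).

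In the analysis, setting is named only in the subgroup part: "Subgroup analyses for setting will be analyzed by assessing interaction effects between type of intervention and setting on the primary outcomes". The article itself calls that part explorative. It neither requires setting in the main model nor expressly excludes it.

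**The concern.** A factor used to stratify randomisation normally belongs in the analysis model. Stratification makes the treatment estimate more precise to the extent that the factor predicts outcome, and the model standard error reflects this only if the factor is in the model.

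Here the factor must pass a change-in-estimate test. Such a test responds to imbalance between arms, and stratified blocks are there to prevent that imbalance. The better the stratification works, the more likely the rule is to discard the factor. The threshold is also relative to the estimated effect, so whether setting is in the primary model depends partly on the result.

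At stake are confidence intervals somewhat wider than the design warrants, a test that runs below its nominal 5%, and an avoidable data-dependent choice in the primary analysis.

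**Working it through.** **Inputs from the article (Sample size, Randomisation, Data analyses).** Pain SD 20 on a 0-100 scale; difference sought 10; WOMAC SD 16 and difference 8 (effect size 0.5 in both cases); 80% power; 5% alpha, taken as two-sided; 5% loss; total 135; blocks of 2 and 4 within two strata.

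**Assumptions, because the article gives no figure.** The difference in mean pain between general practice and orthopaedic patients (the gap) is 0, 5, 10 or 20 points. The general-practice share is 50% (also 30% in the simulation).

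**Step 1: the plan's own figure.** n per arm = 2 × (1.960 + 0.842)² × (20/10)² = 62.8, so 63 by the normal approximation. The t-test solution is 63.77, so 64. 128/0.95 = 134.7, so 135. Both stated figures reproduce.

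**Step 2: how far setting can move the estimate.** With blocks of 2 and 4, each stratum can be out of balance by at most 2 patients. With 135/2 = 67.5 per arm, the arms' general-practice shares differ by at most about 2/67.5 = 0.0296. The largest shift is 0.0296 × gap: 0.15, 0.30 or 0.59 points for a gap of 5, 10 or 20. At the planned effect the threshold is 10% of 10 = 1 point. This bound holds for patients as randomised; loss to follow-up can loosen it.

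**Step 3: how often setting passes the rule.** Simulation of 135 patients, stratified blocks of 2 and 4, total SD 20, one time point, linear model with and without setting, 3,000 runs per scenario. Percentage of trials in which setting enters, with 5% loss (general-practice share 30% / 50%):

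| Gap | True effect 10 | True effect 5 | No effect |
|---|---|---|---|
| 0 | 0.3 / 0.3 | 4.6 / 3.7 | 11.1 / 10.4 |
| 5 | 0.6 / 0.8 | 7.1 / 7.2 | 17.4 / 19.6 |
| 10 | 1.2 / 1.2 | 14.1 / 15.3 | 32.9 / 35.0 |
| 20 | 4.6 / 6.4 | 30.2 / 32.2 | 56.0 / 59.2 |

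Without loss the ranges are 0.1-0.4% (effect 10), 1.6-13% (effect 5) and 4-42% (no effect). At the planned effect, setting is therefore omitted in about 94-99.9% of trials.

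**Step 4: the cost when setting is omitted.** Equal split, 64 per arm, no baseline adjustment.

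- Share of variance due to setting: R² = 0.25 × gap²/20².
- Ratio of reported to true standard error: f = 1/√(1 − R²).
- Actual alpha: 2 × (1 − Φ(1.96 f)).
- Reported standard error: 20 × √(2/64) = 3.536, so effect/SE = 10/3.536 = 2.828.
- Power without setting: Φ((2.828 − 1.96) f). Power with setting: Φ(2.828 f − 1.96).

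| Gap | R² | SE too large by | Alpha | Power without | Power with | Loss (points) |
|---|---|---|---|---|---|---|
| 0 | 0 | 0% | 0.050 | 80.7% | 80.7% | 0 |
| 5 | 0.016 | 0.8% | 0.048 | 80.9% | 81.3% | 0.4 |
| 10 | 0.0625 | 3.3% | 0.043 | 81.5% | 83.2% | 1.7 |
| 20 | 0.25 | 15.5% | 0.024 | 84.2% | 90.4% | 6.2 |

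**Step 5: type I error when the 10% rule is actually applied.** In the simulation with 5% loss it is about 0.042 at gap 10 and 0.031-0.034 at gap 20, against about 0.05 with setting always in the model. The simulation error at 5% is √(0.05 × 0.95/3000) = 0.004.

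**Step 6: if baseline pain is in the model.** Assume the same gap at both visits and a baseline to week-2 correlation r. The residual variance is 1 − r² without setting. With setting it is (1 − R²)(1 − ρ²), where ρ = (r − R²)/(1 − R²). For r = 0.5 and R² of 5% or 10%, the standard error is 0.9% or 1.9% too large, alpha is 4.8% or 4.6%, and the power loss is 0.3 or 0.6 points. For r = 0.3, alpha is 4.7% or 4.3% and the loss is 0.7 or 1.4 points.

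**The case against.** Several points on the other side stand.

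- **Setting is not always excluded.** A reader might infer from Step 2 that it can never be selected. The documents do not support that: the rule is relative to the estimate, so a small or null effect lowers the threshold, and the anticipated 5% loss can unbalance strata beyond the block limit. The table in Step 3 shows both effects.
- **The mismatch is conditional.** A reader might also infer that the standard errors are wrong as a matter of fact. They are wrong only if setting predicts week-2 pain, and the article gives no figure for that. Both settings share the same entry criteria, including a pain score of at least 3 despite oral medication. An R² of 5-10% would need a gap of √(0.05 × 400/0.25) = 8.9 to √(0.10 × 400/0.25) = 12.6 points, about the size of the treatment effect sought.
- **The arithmetic is simpler than the planned model.** Steps 2 to 5 use one time point and no baseline pain, whereas the plan is a repeated-measures model. Step 6 shows that the loss shrinks if baseline pain is modelled, though the article does not say how baseline pain is used.
- **The error is on the safe side.** No false-positive risk is added.
- **A fuller plan may name setting.** The reference to covariates does not rule it out. This answers only in part: the article does state both the model terms and the selection rule, and as stated they suit a stratification factor badly. If a separate analysis plan already forces setting in, the two texts need aligning.

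**Conclusion.** The point holds in a limited form. The article stratifies by setting, then leaves setting's place in the main model to a rule that is the wrong test for it. At the planned effect the rule will usually omit setting; at smaller effects, whether it enters depends on the data.

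The cost depends on an unknown gap. It is nil with no gap, slight at 5 points, modest at 10, and material only at 20 points, which is a whole SD. These sizes rest on SD 20, an equal split and a single time point without baseline pain, and they are smaller if baseline pain is modelled.

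It should not be read as a threat to validity. The test is conservative, unadjusted power at 64 per arm stays above the planned 80% in every scenario examined, and the 64 per group and 135 in total are unaffected. The case for change is that the remedy is almost free and removes a result-dependent choice from the primary analysis.

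**What to change.** Add one sentence to Data analyses: setting is a fixed covariate in the linear mixed models for the primary and secondary outcomes, whether or not it meets the 10% criterion. Keep the setting-by-therapy interaction as the exploratory analysis already described.

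For the GEE models of dichotomous outcomes, include setting as well and note that the odds ratio is then conditional on setting, so it is not the same quantity as the unadjusted one. The calculations above are for linear models and do not give the size of the effect there.

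The cost is one sentence and one degree of freedom. No new data and no change to the sample size are needed.
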